### Participant timeline

**Table 2 Tab2:**
[figure not shown]
Time schedule of enrolment, interventions, and assessments

### Data collection

For the SAS, FIRST, TCM rating scale of Gastrointestinal symptoms, GSRS, safety evaluation of electroacupuncture and evaluation of the resistance towards electroacupuncture, the questionnaires will be done in Case Report Form (CRF). Three scale questionnaires shall be filled by the patients themselves or under assistance of appointed data collectors according to the participant timeline (Table 2). Participants will complete the first questionnaire before the first treatment, while the second and the third questionnaire shall be collected after the treatment on the 3rd and 5th day respectively. Data collection will be done by data collection team instead of the acupuncturists to ensure neutrality of the results.

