### Blinding

According to the principle of blinding, group allocation information will be withheld from the subjects, data collection team and the statisticians. The subjects of both groups are blinded with the subjects in the control group receive placebo electroacupuncture therapy. Due to the profession of acupuncture techniques and the particularity of acupoints, the acupuncturists could not be blinded. They will be requested to perform the treatment according to the allocation and record any adverse events but will not assess the efficacy of the treatment. The data collection team is blinded. The team members will not be informed of the group allocation and will only be responsible for collecting data from the subjects. The statisticians are blinded. They are solely responsible for the statistical analysis and data interpretation. Unblinding will be taken if any serious adverse events happen, including serious complications caused by surgeries.

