#### Interventional group – electroacupuncture group (EG)

Participants in the EG will receive electroacupuncture therapy every day for 5 days consecutively, from the first day post-surgery onwards, each session lasts 20 min. Single-use acupuncture needles (diameter 0.30 mm, length 40 mm, China Suzhou Medical Appliance Company 20162200970, Hwato) will be inserted on acupoints Neiguan(PC6), Gongsun(SP4) bilaterally, 4 acupoints in total (Table 1), after the sites of insertion are disinfected. Acupuncturists shall then perform gentle manipulations on all acupoints until muscle twitch responses are sought from participants. Next, paired alligator clips of the electroacupuncture apparatus (China Suzhou Medical Appliance Company 20172200710, Hwato) are attached at bilateral acupoints (PC6 to SP4, lengthwise), with a continuous wave of 10 Hz and a current intensity of 0.5 mA to 2 mA, depending on the patient’s tolerance level. The location of acupoints is referenced from “Nomenclature and Location of Acupuncture Points” (GB/T 12346 − 2021).

**Table 1 Tab1:** Locations of Neiguan (PC 6) and Gongsun (SP 4)

Acupoints	Locations	Depth of insertion
Neiguan (PC 6)	On the palmar aspect of the forearm, 2 cun above the transverse crease of the wrist, between the tendons of m. palmaris longus and m. flexor carpi radialis.	15–30 mm, vertically
Gongsun (SP4)	On the medial aspect of the foot, in the depression distal and inferior to the base of the first metatarsal bone	15–25 mm, vertically

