#### Control group – placebo group (PG)

Participants in the PG will similarly receive electroacupuncture therapy every day for 5 days consecutively, from the first day post-surgery onwards, each session lasts 20 min. However, needles are applied on non-acupoints (1 cm apart from the acupoints of EG), with no needle manipulations performed(Fig. 2). To ensure the implementation of blinding, electrodes are attached, with a continuous wave of 10 Hz, but a lower current intensity of 0.1 mA.

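### The team declared blinded also collects the form on tolerance of electroacupuncture, which may reveal the arm to collectors who may help patients with the subjective scales

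*Protocol article*

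**What the plan says.** All references are to the protocol article.

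- **Data collection** lists the four scales (SAS, FIRST, TCM scale, GSRS) and the "safety evaluation of electroacupuncture and evaluation of the resistance towards electroacupuncture" as questionnaires held in the case report form. It then states: "Data collection will be done by data collection team instead of the acupuncturists to ensure neutrality of the results". No exception is made for the last two items.
- The same section allows help with completion: "Three scale questionnaires shall be filled by the patients themselves or under assistance of appointed data collectors". The first questionnaire precedes the first treatment; the second and third follow treatment on days 3 and 5.
- **Data management** has the assessors record data on paper forms.
- **Blinding** describes the safeguard for this team: "The team members will not be informed of the group allocation and will only be responsible for collecting data from the subjects". It also asks the acupuncturists, who are not blinded, to record adverse events.
- **Safety evaluation** counts intolerance to electroacupuncture as an adverse event, found through patient reports and assessments by medical workers.
- **Interventions:** in the electroacupuncture group, needles are manipulated until the muscle twitches, with "a current intensity of 0.5 mA to 2 mA" set to the patient's tolerance. In the placebo group there is no manipulation; electrodes are attached, "but a lower current intensity of 0.1 mA".

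**The concern.** Withholding the allocation list from the collectors does not stop them inferring the arm from what patients report. A form about how the patient tolerated the stimulation touches the very feature on which the arms differ. If a collector reads or hears those answers and later helps the same patient with an anxiety, sleep or symptom scale, the help is no longer given blind. Assisted answers could then drift towards the arm expected to do better, and the neutrality that the article gives as the reason for using a separate team would not be secured for those scales.

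This route is distinct from participants guessing their own treatment, which the Discussion already acknowledges. Here the information reaches the assessor through the trial's own paperwork.

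**Working it through.** **Step 1. Does the text create the route?** It needs three links.

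| Link | Source | Status |
|---|---|---|
| The blinded team handles the tolerance form | Data collection, Data management, Blinding | Plain reading of the text, but the handling of intolerance as an adverse event points elsewhere (Blinding, Safety evaluation) |
| The answers carry information on the arm | The two intervention sections | Plausible: twitch against no manipulation, and placebo current at 0.1/0.5 = 1/5 to 0.1/2 = 1/20 of the active current. The form's items are not shown |
| The form is seen before an assisted scale is completed | Data collection, Table 2 | Unknown: the text dates only the scales, and Table 2 is not shown |

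**Step 2. How well could a collector guess?** The documents give no rates, so these are assumptions. Let *s* and *f* be the shares reporting a strong sensation in the active and placebo arms. With 1:1 allocation, guessing from that answer is right with probability p = 0.5s + 0.5(1 − f).

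| s | f | p |
|---|---|---|
| 0.05 | 0.05 | 0.50 |
| 0.10 | 0.02 | 0.54 |
| 0.30 | 0.10 | 0.60 |
| 0.50 | 0.10 | 0.70 |
| 0.80 | 0.10 | 0.85 |

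The possible loss of blinding runs from none to large.

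**Step 3. What would that do to a scale?** Assume a share *a* of forms is assisted, and that correct knowledge of both arms would move assisted scores apart by δ SD. A wrong guess moves a score the opposite way, so:

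bias = a × δ × (2p − 1).

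Assumed low, middle and high cases at p = 1: 0.25 × 0.2 = 0.05 SD; 0.50 × 0.3 = 0.15 SD; 0.75 × 0.4 = 0.30 SD.

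With no true effect, the rejection rate of a two-sided 5% t-test follows from a noncentral t with noncentrality bias × √(n/2). For n = 52 per arm (Sample size section), √26 = 5.10:

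| a × δ | p = 1 | p = 0.85 | p = 0.70 | p = 0.60 | p = 0.50 |
|---|---|---|---|---|---|
| 0.05 SD | 5.7% | 5.4% | 5.1% | 5.0% | 5.0% |
| 0.15 SD | 11.8% | 8.3% | 6.1% | 5.3% | 5.0% |
| 0.30 SD | 32.9% | 18.6% | 9.3% | 6.1% | 5.0% |

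With 44 per arm (52 × 0.85 = 44.2 after the stated 15% dropout), the p = 1 column becomes 5.6%, 10.7% and 28.5%.

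The plan states no figure on this point, so there is none to reproduce.

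**The case against.** The strongest reply is that much of the chain is not in the text.

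- *The answers identify the arm.* A reader might infer this from the difference in stimulation. The documents do not show it. The form's items are unseen, the active current is set to tolerance, and placebo patients also have needles and electrodes, so recorded intolerance could be low in both arms. This stands: the answers may reveal the arm, no more.
- *The form comes before the later assisted scales.* This too might be inferred. If tolerance is recorded once, after the day 5 scales, the route reaches none of them. This stands, because Table 2 is not shown.
- *All four scales are affected.* The assistance sentence speaks of three scale questionnaires, although four scales are named. It may mean three scales or three occasions. Patients may also complete them unaided.
- *The blinded team handles safety.* The text does not settle this. The Blinding section gives adverse event recording to the acupuncturists, and Safety evaluation counts intolerance as an adverse event. This weakens any certainty about who sees the information, and is itself a reason to clarify.
- *The main result is at risk.* Not by this route directly: doctors record first flatus time.
- *Form order is detail that an article leaves to the full protocol.* Partly fair. However, the article itself assigns the form to the team and relies on that team's neutrality, so the point does not rest on silence alone.

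**Conclusion.** The point holds as a risk created by the stated allocation of tasks, not as a demonstrated loss of blinding. As written, one team is declared blinded, collects the tolerance form and may help with subjective scales, and no stated safeguard separates these tasks.

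The size is unknown. Under the assumptions above, the false-positive rate on an affected scale runs from the nominal 5% to about 33%. The top requires 75% of forms assisted, a 0.4 SD shift and perfect guessing. At 50% assisted and 0.3 SD it is about 12% with perfect guessing, but 6.1% when 70% of guesses are right. These figures illustrate the mechanism and are not estimates for this trial. The reach is limited to assisted, patient-reported secondary scales. The change is worth making because it costs almost nothing.

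**What to change.** In Data collection:

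1. State that at each assessment SAS, FIRST, the TCM scale and GSRS are completed before any tolerance or safety question.
2. Have the participant complete the tolerance form alone, on a separate sealed sheet that the efficacy data collectors do not read. Sealing should apply to those collectors only: withholding all tolerance data until database lock would clash with the handling of intolerance as an adverse event, and passing the form to the acupuncturists would clash with the article's own reason for a separate team.
3. Reconcile Blinding, Data collection and Safety evaluation on who records intolerance as an adverse event, so that safety reporting continues in real time outside the efficacy collectors.
4. Add a self-completed / assisted tick-box to each scale, so that the share of assisted forms is known and can be compared between arms.

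Order matters as well as separation: answers on day 3 could still inform a collector on day 5, so step 1 alone is not enough. Nor does the set close the route fully, since patients may mention sensations in conversation.

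Cost: a re-ordered form, one extra sheet and a few sentences; no added visits or patients. The small downside is that the collectors cannot check the tolerance sheets for completeness.

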### Data management

Data will be recorded on CRFs in paper form by the assessors. All original data will be stored in the medical record room of the Shanghai Seventh People’s Hospital for 3 years under the supervision of the Ethics Committee of Shanghai Seventh People’s Hospital affiliated to Shanghai University of Traditional Chinese Medicine.

### Statistical analyses

Data is analysed on the intention-to-treat (ITT) principle using all randomized participants. SPSS 25.0 is used to analyse data, with the statistical significance set at *P* < 0.05. Normally distributed continuous variables will be represented by mean and standard deviation (‾*x ± s*), and will be analysed using independent-samples *t*-test, whereas comparison of data within groups is done through paired *t*-test. Continuous variables that do not follow a normal distribution will be represented by median (quartiles), and will be analysed using the non-parametric test. Enumeration data will be analysed using the χ2 test. Categorical variables are analysed using a rank-sum test. Repeated measure ANOVA test will be used for statistical data recorded at multiple time points.

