### Sample size

This randomized controlled trial aims to explore the improvement in the first flatus time of post-surgery patients on electroacupuncture therapy compared to placebo therapy. Based on a previous study conducted in China [18], sample size was calculated with 80% power and two-tailed α = 0.05, β = 0.20, taking the ratio of 1:1 for the interventional group and control group. Assuming a dropout rate of 15%, this study requires 52 subjects in each group, with a total of 104 subjects to be recruited.

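### Repeated-measures ANOVA for the secondary scales drops participants with a missing form and names no baseline adjustment; a baseline-adjusted mixed model fits the intention-to-treat aim better

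*Protocol article*

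**What the plan says.** The Statistical analyses section of the protocol article sets the population: "Data is analysed on the intention-to-treat (ITT) principle using all randomized participants". It names the software ("SPSS 25.0 is used to analyse data, with the statistical significance set at" P < 0.05) and, for repeated data, the method: "Repeated measure ANOVA test will be used for statistical data recorded at multiple time points". Between-group comparisons of normally distributed variables use an independent-samples t-test, "whereas comparison of data within groups is done through paired" t-tests.

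The Data collection section fixes three rounds of the scales. "Participants will complete the first questionnaire before the first treatment", and "the second and the third questionnaire shall be collected after the treatment on the 3rd and 5th day respectively".

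The Sample size section expects incomplete follow-up: "Assuming a dropout rate of 15%, this study requires 52 subjects in each group, with a total of 104 subjects to be recruited".

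The article does not say whether the pre-treatment score is a level of the time factor or a covariate, which ANOVA term is the treatment test, or how missing forms are handled.

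**The concern.** Three stated choices sit badly together: a method that needs a complete row per participant, an analysis set of everyone randomised, and an expected dropout of 15%. Under the Discontinuation criteria and Safety evaluation sections, participants may leave because of severe complications, adverse events or intolerance of the treatment. Those lost need not resemble those who stay, so deleting incomplete cases could bias the comparison as well as weaken it.

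One of the three rounds is a pre-treatment measurement, at which randomisation makes the expected difference between arms zero. Analysed as an ordinary time point, it dilutes the group main effect. Used as a covariate, it sharpens the comparison.

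A paired test within one arm does not estimate a treatment effect. Patients recovering from surgery are likely to change in both arms, so a significant change in one arm and not the other can be misread as efficacy.

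**Working it through.** **Inputs from the protocol article.** 104 participants, 52 per arm, 15% dropout, "sample size was calculated with 80% power and two-tailed α = 0.05, β = 0.20, taking the ratio of 1:1" (Sample size); three rounds of forms (Data collection); method, software and population (Statistical analyses).

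**Assumptions, none from the documents.** Equal variance, set to 1, at each round; compound symmetry with correlation r of 0.5 to 0.6 (wider range 0.3 to 0.7); the same effect D on days 3 and 5 and zero at baseline; illustrative missingness of 5% or 10% per form.

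**The plan's own figure.** The 52 per arm cannot be re-derived, because neither a difference nor a standard deviation is given. Only the dropout step can be checked: 44 / (1 − 0.15) = 51.8, which rounds up to 52. (45 × 1.15 = 51.75 also gives 52.) This size was set for first flatus time; no size or power is stated for the scales.

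**Step 1: who is analysed.**
- Protocol dropout, every dropout lacking a form, no imputation: 104 × 0.85 = 88.4, about 88.
- Independent missingness m per form gives (1 − m)³ complete. At 5%: 0.95³ = 0.857, about 89 of 104. At 10%: 0.90³ = 0.729, about 76 of 104. Independence is doubtful over five treatment days, and the 27% loss in the second case exceeds the protocol's own 15%, so the 88 is the better anchor.
- At least one post-baseline form, same missingness: 1 − m² = 0.9975 and 0.99, about 104 and 103 of 104.
- If a missing baseline also removes the participant: (1 − m)(1 − m²) = 0.948 and 0.891, so about 5% and 11% are still lost.
- Timing matters. If all dropouts leave after the day-3 form, a model using any post-baseline score keeps all 104. If all leave before it, a model with baseline as a covariate analyses the same 88.

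**Step 2: use of baseline.** Variances are per participant, in units of the score variance.
- Group main effect over three rounds: estimates (0 + D + D)/3 = 2D/3, with variance (1 + 2r)/3.
- Mean of days 3 and 5 minus baseline: estimates D, with variance (1 + r)/2 + 1 − 2r = 1.5(1 − r).
- Mean of days 3 and 5 adjusted for baseline: estimates D, with variance (1 + r)/2 − r².

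| r | Adjusted variance | Contrast variance | Contrast efficiency | Main-effect efficiency |
|---|---|---|---|---|
| 0.5 | 0.75 − 0.25 = 0.50 | 0.75 | 0.50/0.75 = 67% | (4/9) × 0.50/0.667 = 33% |
| 0.6 | 0.80 − 0.36 = 0.44 | 0.60 | 0.44/0.60 = 73% | (4/9) × 0.44/0.733 = 27% |

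Over the wider range, contrast efficiency runs from 0.56/1.05 = 53% at r = 0.3 to 0.36/0.45 = 80% at r = 0.7. For day 5 alone, change from baseline has variance 2(1 − r) against 1 − r² adjusted. The relative efficiency is (1 + r)/2, or 75% at r = 0.5 and 80% at r = 0.6.

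As a power illustration, take an assumed effect of 0.5 SD, 44 complete cases per arm and r = 0.3 / 0.5 / 0.7. The omnibus group-by-time test has power 52 / 67 / 88%, against 88 / 91 / 97% for the baseline-adjusted comparison.

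**Step 3: paired tests.** With no difference between arms, if each arm's paired test has probability p of significance, exactly one arm is significant with probability 2p(1 − p): 42%, 50% and 32% at p = 0.3, 0.5 and 0.8.

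**The case against.** Several stronger readings are tempting, and the article does not support them.

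- **That the plan contradicts intention-to-treat outright.** The conflict needs missing forms and no imputation. The article states no missing-data rule, and a fuller protocol or analysis plan may contain one. What stands is a poor fit between the named method and the stated population.
- **That the plan treats baseline as an outcome and so wastes it.** Baseline as a level of the time factor is an inference. The SPSS repeated-measures procedure also accepts a baseline covariate. Even on the natural reading, the group-by-time test uses baseline and is valid; it is only less efficient.
- **That the analysis keeps only 27–33% of the available efficiency.** This holds for the group main effect alone. The usual treatment test when baseline is a time level is group-by-time, where the figure is 67–73%.
- **That the paired tests will be used to claim efficacy.** The article says no such thing and names the between-group test first. The risk is misreading, which a label removes.

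It is also fair to say that a mixed model is not a complete cure. It cannot recover treatment information from someone with no post-baseline score, and with baseline as a plain covariate it drops anyone lacking that form. It still improves on complete-case deletion whenever some participants have a partial record, and it uses baseline more efficiently even when no form is missing.

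**Conclusion.** The point holds for SAS, FIRST, the TCM symptom scale and GSRS. The named procedure would analyse about 88 of 104 at the protocol's own dropout rate, provided every dropout lacks a form and nothing is imputed. No baseline adjustment is named. If baseline is a time level, the main effect is diluted to two thirds, and the valid post-minus-baseline contrast has about 67–73% of the efficiency of a baseline-adjusted comparison. That range rests on compound symmetry, an assumed correlation of 0.5–0.6 and a constant effect on days 3 and 5.

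This is a worthwhile improvement to secondary analyses, not an invalidating error. The primary outcome, first flatus time, is not a repeated measure and is unaffected. The baseline argument does not extend to QoL-C30, for which the text gives no pre-treatment value. The schedule of laboratory tests is in a table that is not shown, so nothing is concluded about them.

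**What to change.** For the four scales, replace repeated-measures ANOVA with a likelihood-based mixed model (SPSS MIXED, unstructured covariance). Days 3 and 5 are the outcomes; baseline score, arm, time and arm-by-time are the fixed effects. Keep participants whose baseline form is missing, either by a simple imputation of baseline or by a model that includes baseline in the response with its mean constrained equal across arms. Name the day-5 between-group difference with its 95% CI as the treatment test. State how many randomised participants contribute no post-baseline score. Label the within-group paired t-tests as descriptive and not as evidence of efficacy.

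The cost is a change of wording and slightly more analysis work, with the same software and the same data. The Trial status section plans analysis from July 2026, so the change should be recorded before then.

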### Data monitoring and quality control

A Quality Control Team is instituted with the responsibility of conducting regular or ad-hoc monitoring visits and ensuring data accuracy within the research team. An independent assistant will oversee the data collection process, while the Ethics Committee of the Shanghai Seventh People’s Hospital will undertake periodic reviews. In the event of any deviations from the established protocol during monitoring, the researcher is mandated to meticulously document the deviation, outlining the time of discovery, procedural details, underlying reasons, and the corresponding corrective measures. The researcher is required to endorse this record, and the study shall be suspended.

During the statistical analysis phase, two independent study assistants are designated to input the data. They conduct self-checks to identify any discrepancies in the inputted data and promptly rectify any errors detected. Furthermore, these assistants are tasked with analysing, assessing, and reporting on the potential impact of any protocol deviations on the final data and conclusions.

